### Intervention

2.4

This intervention aims to integrate an ABI screening program into the current CHD risk assessment in the primary care setting. We will use the prediction capacity of the REASON risk model to select the best candidates for ABI measurement in individuals aged 50–74 without previous CVD.

The whole intervention process is illustrated in Figure 1. During a routine primary care visit, individuals who meet the inclusion criteria will undergo the CHD risk assessment with REGICOR. If their REGICOR score is ≥ 7%, we will calculate their probability of having a low ABI, ≤ 0.9, using the REASON risk function. Individuals with a predicted probability of low ABI ≥ 7% will be the candidates for an ABI measurement performed by a trained health professional.

**Figure 1 fig1:**
[figure not shown]
Diagram of the HELENA study protocol. CHD, Coronary heart disease; ABI, Ankle-brachial Index; PAD, Peripheral artery disease.

The CHD risk of individuals with ABI results ≤ 0.9 will be reclassified. According to a previous meta-analysis, individuals with an ABI ≤ 0.9 have at least twice the 10-year total mortality, CV mortality and major coronary event rates compared to individuals with normal ABI values (7). Therefore, in individuals with an ABI ≤ 0.9, the initial REGICOR risk score will be doubled, and the patient reclassified into a high or very high CHD risk group.

Subsequently, physicians will provide recommendations based on the Catalan Health Institute’s Guidelines about Lipids and Cardiovascular Risk (18). For asymptomatic patients with ABI ≤ 0.9, the recommendations are as follows: (1) healthy lifestyle modifications: encourage healthy lifestyles such as regular physical activity (at least 30 min per day of moderate physical activity), adhesion to Mediterranean diet reduction of saturated or trans fats, daily consumption of fruits and vegetables, and consumption of fatty fish 2 days per week, weight management, reduction of alcohol consumption, and smoking cessation; (2) medication: use of moderate-intensity statin treatment based on individual CHD risk score. For high CHD risk score use simvastatin 20 mg/dL, atorvastatin 10 mg/dL, or pravastatin 40 mg/dL. For very-high CHD risk score, use simvastatin 40 mg/dL, or atorvastatin 20 mg/dL; (3) control of CVD risk factors: hypertension, diabetes, and hyperlipidemia. Patients with ABI > 0.9 should follow the recommendations of the guidelines based on the estimated CHD risk (Figure 1).

#### Pilot study

2.4.1

To assess key factors that could challenge the intervention implementation or would ensure its success, we conducted a pilot study over 2 weeks in March 2023 in 17 primary care centers. This study was supported by a group specialized in implementation research. Data on factors that ensured a successful implementation were collected via questionnaires and focus groups from health professionals. Participants in this pilot highlighted the importance of being familiar with the Catalan Health Institute’s Guidelines on Lipids and Cardiovascular Risk, and acquiring the necessary skills for the new screening program. Health professionals also emphasized the importance of effectively conveying the benefits of the screening program. Moreover, effective planning and organization within each center were identified as pivotal factors for the implementation of the intervention.

This information was used to develop a strategy for the adoption of the new CHD screening program. The strategy was based on the following main elements: (1) commitment to a common goal: a series of workshops and training sessions were organized to raise awareness of the new procedure; a representative of the health professionals was designated in each center to emphasize the life-saving potential of the new screening strategy; (2) collaborative organizational action: each center was encouraged to define a workflow considering the workload of the professionals and their available resources; (3) need for tension to prompt change: regular feedback loops were established to discuss project challenges and early results; performance monitoring variables were also integrated into the EHR and reviewed during the feedback sessions to maintain collective commitment; (4) sustainability of the intervention over time: to ensure sustainability, periodic sessions and updates were planned with the representatives of each center.

### Data collection and management

2.5

This is a pragmatic clinical trial. Basic and monitoring data will be generated from the regular clinical practice; afterwards, the generated data will be extracted from the EHR. The following data will be collected:

#### Cardiovascular risk variables

2.5.1

We will use the REGICOR’s and REASON’s function scores; and the variables used for its calculation: age, sex, systolic and diastolic blood pressure, diabetes, tobacco consumption, total and HDL cholesterol; and ABI’s result if it is measured.

#### Monitoring and result variables

2.5.2

Monitoring of the patients’ data will occur every 3 months during the first semester of the study to assess the implementation. After that, it will be conducted every 6 months up to 3 years from the patients’ study enrolment.

The study primary outcomes will be hard CHD (myocardial infarction, cardiac revascularization, or coronary death); major adverse cardiovascular events (MACE), a composite of hard CHD and stroke (fatal and nonfatal ischemic stroke); all-cause mortality; and variables related to the assessment of CVD risk factors improvement: tobacco consumption, lipid profile, systolic and diastolic pressure, weight, height, body-mass index (BMI), glycemia, glycated hemoglobin (in patients with DM), creatinine, proteinuria, albumin-to-creatinine ratio, and glomerular filtration rate.

The secondary outcomes will be CHD (a composite of angina and hard CHD), cerebrovascular disease (a composite of stroke [fatal and nonfatal ischemic stroke] and transient ischemic attack); CVD (a composite of MACE, angina, and transient ischemic attack); lipid lowering medication adverse effects: short-term effects (muscular and hepatic alterations) and long-term effects (diabetes and cancer).

The considered potential confounding variables included sociodemographic information: age and sex; PHC related variables: attendance rate, billing rate, and length of time in the EHR; alcohol consumption; comorbidities: diabetes, atrial fibrillation, heart failure, dementia, endocrine and metabolic conditions, inflammatory diseases, asthma, chronic obstructive pulmonary disease, depression, CVD incidence rate; other comorbidities identified in the bivariant analysis; used medication: corticosteroids, antidepressants, hormonal substitutive therapy, oral contraceptives, antipsychotics, anti-inflammatories, Platelet aggregation inhibitors (other than heparin), antihypertensives, anti-diabetic drugs, and lipid lowering medication; laboratory related variables: alanine transaminase (ALT) and aspartate aminotransferase (AST). We will also record health-care quality standards of health care providers and a deprivation index (MEDEA index) (16).

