**Methods:**

This study is a pragmatic randomized cluster trial. A total of 274 primary care centers will be randomized into two groups that will either maintain the current CHD risk detection strategy or add a screening program to detect asymptomatic PAD using ABI. In routine clinical practice, 10-year CHD and PAD risk are assessed using the Framingham-adapted (REGICOR) function and the REASON function, respectively. The study population will consist of patients aged 50 to 74 years with a CHD risk ≥ 7% and PAD risk ≥ 7%, making them candidates for an ABI measurement. Cases with an ABI result ≤ 0.9 will have their CHD reclassified as high or very high by doubling the initial REGICOR score and receive the recommendations of the lipid and cardiovascular risk guideline. The primary outcomes will be hard CHD, major adverse cardiovascular events (MACE), all-cause mortality, and improvement in CVD risk factors. Secondary outcomes include CHD (a composite of angina and hard CHD), cerebrovascular disease, and adverse effects from lipid-lowering medication. Survival analysis will estimate the effectiveness of adding the ABI screening strategy, with Cox models (intention-to-treat) and marginal structural models controlling for confounding variables.

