### Sample size

2.3

The incidence of CV events (coronary or cerebrovascular disease, or symptomatic PAD) is expected to be 7% in the selected population during a period of 3 years. Accepting a 0.05 alpha risk and a 0.2 beta risk in a bilateral contrast, 20,171 people are needed in each arm, intervention and control groups, to detect a relative risk of 0.9.

Around 500.000 people aged 50–74 years have their CHD risk calculated in Catalonia per year. Out of those, we estimate that 36.000 will present both a REGICOR and REASON score ≥ 7%. Thus, in one and a half years we expect that there will be 54.000 people, 27.000 for each arm.

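### Three event outcomes and 13 risk-factor entries are all called primary, with no principal outcome or order, and the sample size spends its single 0.05 on a composite that is not one of them

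*Protocol article*

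**What the plan says.** Section 2.5.2 (Monitoring and result variables) lists the primary outcomes. Three are events: hard CHD, MACE (hard CHD plus ischemic stroke) and all-cause mortality. The same sentence adds "and variables related to the assessment of CVD risk factors improvement: tobacco consumption, lipid profile, systolic and diastolic pressure, weight, height", then BMI, glycemia, glycated hemoglobin in patients with diabetes, creatinine, proteinuria, albumin-to-creatinine ratio and glomerular filtration rate.

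The abstract repeats the primary status in grouped form: "The primary outcomes will be hard CHD, major adverse cardiovascular events (MACE), all-cause mortality, and improvement in CVD risk factors".

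The only significance level is in section 2.3 (Sample size): "Accepting a 0.05 alpha risk and a 0.2 beta risk in a bilateral contrast". It is applied to a composite of coronary disease, cerebrovascular disease or symptomatic PAD, whose incidence "is expected to be 7% in the selected population during a period of 3 years". The target is "to detect a relative risk of 0.9", and the result is that "20,171 people are needed in each arm, intervention and control groups".

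Section 2.6 (Statistical analysis) describes two-group tests, Cox models and marginal structural models. It does not distinguish among the primary outcomes. The Introduction ends with two numbered aims: the first concerns CHD incidence and all-cause mortality, the second CV risk factors.

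**The concern.** A primary outcome is the one on which a trial's claim rests. Here 16 entries hold that status, and nothing in the article says which of them decides the result. The sample size does not settle it, because its composite includes symptomatic PAD, which belongs to none of the listed primaries.

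The list also reads more like a data-collection list than a set of hypotheses. Height cannot improve in adults aged 50 to 74. BMI is computed from weight and height. Lipid profile is not one variable.

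Two things are at stake. First, nothing prevents a difference in, say, creatinine or glycemia from being reported as a positive primary result while hard CHD, MACE and mortality are unchanged. Second, the planned size gives no assurance about any particular listed primary, because it was derived for something else.

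**Working it through.** **Inputs.** Two-sided alpha 0.05, power 0.80, 7% in the control arm, relative risk 0.9 (so 7% × 0.9 = 6.3% in the intervention arm), 20,171 needed and 27,000 expected per arm, all from section 2.3. The outcome list is from section 2.5.2.

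**Step 1: count the primaries.** Events: hard CHD, MACE, all-cause mortality = 3. Risk-factor entries: tobacco, lipid profile, systolic pressure, diastolic pressure, weight, height, BMI, glycemia, glycated hemoglobin, creatinine, proteinuria, albumin-to-creatinine ratio, glomerular filtration rate = 13. Total 16, with lipid profile counted once. If lipid profile is assumed to be four variables, the total is 19.

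**Step 2: reproduce the stated sample size.** With p1 = 0.07, p2 = 0.063, mean p = 0.0665 and d = 0.007:

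n = [1.960·√(2·0.0665·0.9335) + 0.842·√(0.07·0.93 + 0.063·0.937)]² / 0.007² ≈ 19,886, rounded up to 19,887.

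With the continuity correction, n' = (n/4)·[1 + √(1 + 4/(n·d))]² = 20,170.9, rounded up to 20,171. This is the stated figure exactly. A one-sided test would give 15,665 and does not fit. The stated size therefore spends the whole two-sided 0.05 on one comparison.

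**Step 3: family-wise error if any one significant primary may be claimed, independent tests.** FWER = 1 − 0.95^k.

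- k = 3 (events only): 1 − 0.95³ = 14.3%
- k = 4 (the abstract's grouping): 18.5%
- k = 16: 56.0%
- k = 19: 62.3%

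**Step 4: allow for overlap.** Hard CHD lies inside MACE, BMI derives from weight and height, and the renal markers overlap, so independence overstates the error. The article gives no correlations, so they are assumed. With a common correlation ρ between test statistics, U standard normal and c = 1.960:

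FWER = 1 − E{[Φ((c − √ρ·U)/√(1−ρ)) − Φ((−c − √ρ·U)/√(1−ρ))]^k}

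| Assumed ρ | 3 events | 16 entries |
|---|---|---|
| 0 | 14.3% | 56.0% |
| 0.3 | 13.6% | 47.6% |
| 0.5 | 12.5% | 37.4% |
| 0.7 | 10.9% | 26.4% |
| 0.9 | 8.4% | 14.6% |

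With correlation only within related groups (hard CHD and MACE; the two pressures; weight, height and BMI; the two glucose measures; the four renal markers), simulation of the 16 tests gives 52% at a within-group correlation of 0.5 and 43% at 0.9. Leaving height out (k = 15) changes little: 53.7% independent, 14.4% at ρ = 0.9.

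**Step 5: could the planned size absorb a split of alpha?** Using the Step 2 formula without continuity correction, at 7% and relative risk 0.9:

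| Bonferroni over | Alpha per test | Per arm for 80% power | Power at 20,171 | Power at 27,000 |
|---|---|---|---|---|
| 3 events | 0.0167 | 26,526 | 66.6% | 80.8% |
| 16 entries | 0.003125 | 36,525 | 44.7% | 62.1% |

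These rows borrow the 7% of the sized composite. Hard CHD and MACE are narrower, so at the same relative risk their power would be lower. Like the stated figure, the rows make no allowance for clustering.

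**The case against.** **The SAP may control multiplicity.** It may, and the absence of a procedure from an article is not the complaint. Which outcomes are primary is stated in this document, and so is the composite used for sizing. An SAP can order or adjust the 16 entries. It cannot make the sized composite one of them, and Step 5 shows that an equal split over 16 would not fit the expected 27,000 per arm.

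**No rule says that one significant result is enough.** This stands. A reader might infer that any primary with p < 0.05 counts as a positive trial, but the article says no such thing. It states 0.05 only for the sample size and gives no success rule. If all primaries had to succeed, the type I error would not be inflated at all. The inflation is therefore conditional: the text leaves that reading open and does not exclude it.

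**The risk factors serve a separate second aim.** This also stands in part. A creatinine result would answer aim 2, not aim 1, and hard CHD is defined and listed first. So a reader should not conclude that the CHD question has no outcome. But a second aim does not need 13 separate primary variables, and no combined risk-factor measure is defined.

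**56% is too high.** As an estimate it is, because it needs 16 independent tests. The range in Step 4 is the fairer statement. Even the abstract's reading, with risk-factor improvement as a single item, gives 18.5% if the four are independent.

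**Conclusion.** The primary set is fixed badly in the article itself, whatever an SAP adds. Sixteen entries are primary without a principal outcome or an order, one of them cannot improve, and the sample size rests on a composite outside the set.

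The size of the problem depends on two assumptions: that one significant primary may be claimed, and how far the test statistics correlate. On the first assumption, the family-wise error for 16 entries is 56% under independence and about 15% to 48% for common correlations of 0.9 to 0.3. For the three event outcomes it is about 8% (correlation 0.9) to 14% (independent). It exceeds 5% in every case computed. These are illustrative ranges, not estimates for this trial.

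It would go too far to say that the plan declares any single p < 0.05 a success, or that the trial's true error rate is 56%.

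**What to change.** 1. Keep only hard CHD, MACE and all-cause mortality as primary, and control them at a two-sided family-wise 0.05. Either use a fixed order set before outcome data are analysed, each outcome tested only if the one before is significant, or use Holm across the three.
2. If a fixed order is used, the sponsor should choose and justify whether hard CHD or MACE comes first. MACE contains hard CHD and so has at least as many events. But aim 1 names CHD, and putting MACE first could leave the CHD question formally untested.
3. Make the risk-factor variables secondary outcomes for aim 2, reported with confidence intervals or Holm-adjusted. Name the components of the lipid profile. Drop height as an outcome; it can still be collected to compute BMI.
4. Restate the power for the outcome tested first, with an event rate for that outcome. The 7% and the 20,171 per arm belong to the wider composite.

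**Cost.** More than wording. Risk-factor results can no longer be called primary, and the stated power may become less favourable. Patient monitoring is dated 2023–2025, so the protocol and registry must document that the change was made before outcome analysis. No new data collection is needed.

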### Statistical analysis

2.6

Quantitative continuous variables will be described with the mean and standard deviation or with the median and the interquartile range; categorical variables will be described with frequencies (%). Continuous variables will be compared using the Student’s t-test or Analysis of variance (ANOVA); Mann–Whitney U or Kruskal-Wallis will be applied when pertinent. Categorical variables will be compared using the Chi-squared or Fisher exact test as needed.

Survival analysis tests will be used to estimate the effectiveness of introducing a screening program using ABI. We will build classical Cox models and marginal structural models to account for confounding and intermediate variables. The reduction of the absolute risk and the number needed to treat (NNT) to prevent one additional event will also be calculated.

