Therefore, we designed a new risk function, derivation of the REgicor and Artper Score fOr aNkle brachial index screening (REASON) (15), to select the best candidates for an ABI measurement. This model improved the prediction of ABI ≤ 0.9 in Spanish patients aged 50–74 who were apparently free of CHD (16), and showed similar sensitivity and improved specificity compared to ISC. Furthermore, the predictive ability of REASON can be modulated by changing the cut-off risk point. This feature can be useful to manage the available resources for CV prevention in each region of the world (15). A cut-off point of 7% has a sensitivity of 68%, a specificity of 72%, and selects 35% of the population as candidates for ABI screening (15). This improvement in predictive capacity translates into a considerable reduction in the number of screened people needed to detect a case with ABI ≤ 0.9. Therefore, by reducing the number of false positives and maintaining the sensitivity, the use of REASON should limit the workload and possible adverse events associated with CHD diagnostic procedures and medical treatments (15).

The adoption of a strategy that combines the current CHD risk estimation with REGICOR and the probability of having an ABI ≤ 0.9 assessed with REASON would detect patients that require an ABI test and improve the CHD risk classification (7, 8, 17). The diagnosis of asymptomatic PAD at an early stage can be a critical opportunity to influence the disease progression, prevent its complications, and control its risk factors. Additionally, early diagnosis can also be a motivation to help patients accept the recommendations and improve lifestyle habits, such as smoking cessation, diet, and increased physical activity.

The study that measured the predictive capacity of REASON for ABI ≤ 0.9 was observational, and thus, further research is needed to validate its results (15). Consequently, we have designed this clinical trial to appraise the effectiveness of REASON:

The aims of this study are: (1) to evaluate the effectiveness of integrating an ABI screening program into the current CHD risk assessment strategy for reducing the incidence of CHD and all-cause mortality among individuals aged 50 to 74, and (2) to evaluate the effectiveness of integrating an ABI screening program into the current CHD risk assessment strategy for mitigating CV risk factors among individuals aged 50 to 74.

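### The only comparison stated for the continuous risk-factor primary outcomes is an unadjusted t-test, ANOVA or rank test, although key baselines are recorded and follow-up values repeat

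*Protocol article*

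**What the plan says.** **Outcomes.** Section 2.5.2 of the protocol article lists, beside hard CHD, MACE and all-cause mortality, a further group of primary outcomes: "variables related to the assessment of CVD risk factors improvement". Apart from tobacco use these are mostly continuous (lipids, systolic and diastolic pressure, weight, BMI, glycemia, renal measures). They are also the whole of aim 2 in the Introduction, which is to evaluate the program "for mitigating CV risk factors among individuals aged 50 to 74".

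**Analysis.** The first paragraph of section 2.6 begins with descriptive summaries and continues: "Continuous variables will be compared using the Student’s t-test or Analysis of variance (ANOVA", then "Mann–Whitney U or Kruskal-Wallis will be applied when pertinent". Categorical variables get Chi-squared or Fisher tests. The second paragraph opens with survival analysis and then says: "We will build classical Cox models and marginal structural models to account for confounding and intermediate variables". The Abstract also places the Cox and marginal structural models under survival analysis.

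**Data.** Section 2.5.1 records the risk scores and their inputs: "age, sex, systolic and diastolic blood pressure, diabetes, tobacco consumption, total and HDL cholesterol". Section 2.5.2 sets repeated extraction: "Monitoring of the patients’ data will occur every 3 months during the first semester of the study to assess the implementation", and then every 6 months up to 3 years. Section 2.5 gives the source: "Basic and monitoring data will be generated from the regular clinical practice".

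**The concern.** The survival models do not apply to a blood pressure or a cholesterol value. The t-test, ANOVA and rank tests are therefore the only comparison the article states that could serve the continuous primary outcomes. Three features of the trial do not fit them.

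- **Baseline.** The outcome is improvement, which is relative to a starting value. Blood pressure, total and HDL cholesterol and smoking must be known at entry, because REGICOR and REASON are computed from them. None of the named tests adjusts for them.
- **Repeated values.** Extraction every 3 and then every 6 months can give several values per patient. A two-group test needs one, and the text does not say which.
- **Who is re-measured.** There is no trial visit, so a follow-up value exists only if routine care produced one. An intervention that reclassifies patients and prompts risk-factor control could change who is tested. If so, an unadjusted comparison of those re-measured compares differently selected groups.

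At stake are the precision, and possibly the validity, of every continuous result under aim 2.

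**Working it through.** **1. The plan's own figure.** Section 2.3 gives 20,171 per arm for 7% against 6.3% (relative risk 0.9), two-sided alpha 0.05, power 80%. The pooled two-proportion formula gives [1.960·√(2·0.0665·0.9335) + 0.842·√(0.07·0.93 + 0.063·0.937)]² / 0.007² ≈ 19,887. With the continuity correction it gives 20,171, an exact match. This figure concerns events and is not in dispute. No SD, effect size or sample size is stated for the continuous outcomes.

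**2. Patient-level variance.** The document gives no baseline to follow-up correlation ρ, so 0.5 to 0.7 is assumed. Variance relative to an unadjusted comparison of follow-up values:

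| Analysis | Formula | ρ = 0.5 | ρ = 0.7 |
|---|---|---|---|
| Follow-up value only | 1 | 1.00 | 1.00 |
| Change score | 2(1 − ρ) | 1.00 | 0.60 |
| Baseline-adjusted | 1 − ρ² | 0.75 | 0.51 |

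Against the follow-up value alone, adjustment removes 25% to 49%. Against a change score the ratio is (1 + ρ)/2, so it removes 25% at ρ = 0.5 and 15% at ρ = 0.7.

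**3. Total variance in a cluster trial.** Section 2.3 expects 54,000 patients and the Abstract gives 274 centers, so 54,000/274 ≈ 197 per center. Assume an intracluster correlation of 0.01; the document states none. In units of the variance under independence:

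- within centers: 1 − 0.01 = 0.99
- between centers: 197 × 0.01 = 1.97
- total: 2.96

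If patient-level adjustment shrinks only the within-center part:

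- ρ = 0.5: 0.25 × 0.99 / 2.96 = 8%
- ρ = 0.7: 0.49 × 0.99 / 2.96 = 16%

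The saving is larger if center-level baselines also correlate with center-level outcomes, because the between-center part then shrinks too.

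**4. Scale.** At 27,000 per arm and treating patients as independent, the difference detectable with 80% power is (1.960 + 0.842)·√(2/27,000) = 0.024 SD. With the total of 2.96 it is 0.024·√2.96 ≈ 0.041 SD. Precision is good either way, so its loss is not the main worry.

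**5. Selective re-measurement: an illustration, not an estimate.** A simulation was run with zero true effect, 60% of controls and 80% of intervention patients re-measured, and log-odds of re-measurement rising by 0 to 0.5 per baseline SD. All of these inputs are invented.

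- Where re-measurement did not depend on baseline, the unadjusted difference was at most 0.005 SD, which is simulation noise.
- Where it did, the difference ran from about 0.01 to 0.13 SD in absolute value.
- Baseline adjustment brought it within 0.003 SD of zero throughout, but only because re-measurement was made to depend on baseline and nothing else.

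This shows that a bias above the detectable difference is possible. It does not show that one will occur.

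**The case against.** The strongest reply is that the quoted sentence is generic. It follows the descriptive summaries, names no outcome or time point, and could serve descriptive tables or the bivariate screening of confounders mentioned in section 2.5.2. An article also commonly leaves outcome models to a fuller document. This stands in part: a reader might infer that the plan rules out any use of baseline for aim 2, and the text does not go that far. Section 2.5.1 says the baseline variables will be used without saying how, and improvement may mean change from baseline. But the section is not silent on continuous variables. It states a method for them, and that method does not suit outcomes it calls primary.

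A reader might also turn 1/(1 − ρ²) into a claim that the simple tests waste the equivalent of 1.3 to 2 times the patients. That holds only for independent patients and an analysis of follow-up values alone. Neither can be assumed here, and steps 2 and 3 of the working show how far the gain shrinks.

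Finally, a reader might take it as given that patients with ABI ≤ 0.9 will be tested more often. Section 2.4 lists recommendations for them but no extra visits or tests, and section 2.5.2 sets one monitoring schedule for everyone. Section 2.5.2 also lists attendance rate as a potential confounder, so contact with care is not overlooked, although a t-test cannot use it. Differential re-measurement remains a plausible inference and no more.

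**Conclusion.** The point holds in a limited form. As written, the continuous primary outcomes would be compared without baseline adjustment, without a rule for repeated values and without a center effect. The precision cost is 25% to 49% of within-center patient-level variance for an assumed ρ of 0.5 to 0.7. In total variance it is about 8% to 16% at an assumed intracluster correlation of 0.01, unless center-level baselines help. Against a change-score test the patient-level gain is no larger than 25% over this range of ρ. With about 27,000 patients per arm this loss alone is modest.

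Selective re-measurement could matter more, but the document gives no basis for sizing it. Baseline recording is explicit only for blood pressure, total and HDL cholesterol and tobacco; for weight, glycemia and the renal measures it is at most implied. The change should be made because it is cheap and covers all the continuous outcomes of aim 2. The present text does not show that the results would be invalid.

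**What to change.** Keep the t-test, ANOVA and rank tests for descriptive tables, and say so. For each continuous risk-factor outcome, name a linear mixed model on the recorded follow-up values with:

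- arm, follow-up window and arm by window;
- the baseline value where recorded, keeping patients without one, for example by modelling baseline as part of the outcome vector;
- REGICOR and REASON scores;
- random effects for center and patient.

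If baseline enters the outcome vector with a mean common to both arms, check that assumption against the observed baselines, since centers rather than patients are randomized. State the contrast in advance as the adjusted mean difference at a fixed window, for example 12 and 24 months, and define which values count toward each window. For tobacco use, fit the logistic analogue with baseline smoking. Report the share of patients measured per arm and window, so that differential re-measurement can be seen.

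The cost is analysis code on data already planned for extraction; the design and data collection do not change. The limit should be written down: the model corrects selective re-measurement only as far as it depends on data in the model, not where tests were prompted by something unrecorded.
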